### Interventional Method

The experimental intervention will be performed in the Emergency Department immediately after randomization. A standard blood pressure cuff will be placed around the non-paretic arm. Patients randomized to RIC will undergo remote ischemic conditioning by four cycles of intermittent, manually induced, upper limb ischemia alternating 5 min of inflation (20 mmHg above the systolic blood pressure) to 5 min of deflation. Patients in the control group will have the blood pressure cuff placed around the non-paretic arm for 40 min but will undergo no inflations. All patients will receive usual care, at the discretion of the investigator and according to available guidelines and standards of care.

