### Sample Size Estimates

In the NINDS trial, the NIHSS percent change in the control group was 15% +/– 35% at 24 h. The median of the NIHSS percent change in absence of treatment is expected to slightly increase, and the standard deviation to slightly decrease, at 72 h, due to stabilization of the neurological deficit. An estimated total sample size of 80 patients (40 patients in each arm) should yield 80% power to detect a clinically significant difference of 20% (40% in treatment vs. 20% in control arm) in the median percent change in NIHSS at 72 h, considering a standard deviation of 30%, at the two-sided statistical significance threshold of *p* = 0.05, when using a Wilcoxon-Mann-Whitney test. The primary null hypothesis is that there is no or negligible difference in clinical benefit between remote ischemic conditioning plus standard medical therapy and standard medical therapy alone.

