### Data Analysis

The baseline patient characteristics of each treatment group will be described as means and standard deviations, medians, and quartiles, for numerical variables, and as frequencies and percentages per class for qualitative variables. Between-group unbalances among baseline characteristics will be considered for adjustment whenever deemed important for the outcome, in which case an adjusted secondary logistic analysis will be performed. The primary analysis of treatment effect on early neurological improvement will be performed using a Wilcoxon-Mann-Whitney test. Secondary analysis of the primary outcome will be performed using a mixed linear regression including treatment, centers, and any unbalanced baseline characteristics. Secondary outcomes will be analyzed using a Wilcoxon-Mann-Whitney test to evaluate treatment effect on early neurological improvement at 24 h or 48 h, and using a logistic mixed model to assess the effect of RIC on secondary variables (i.e., Wong-Baker face pain rating scale, modified Rankin scale, and occurrence of symptomatic intracerebral hemorrhage). The mRS scores will be dichotomized as a good functional outcome (mRS 0–2) and poor functional outcome (mRS 3–6). Wong-Baker Face Pain Rating Scale scores will be dichotomized around medians. Whole blood levels of HIF-1α mRNA and plasma levels of HSP27 in each arm will be represented by histograms. We expect no missing data for the primary outcome since patients will still be hospitalized. In case of missing results, a multiple imputation procedure will be used. Analyses will be conducted with an intention-to-treat approach (ITT). For the primary outcome, patients with neurological worsening will be given a percent change of 0; those deceased within 72 h will be given the last percent change available and a percent change of 0 will be assigned in case admission NIHSS is the only available data. A population of interest is composed of patients that completed the experimental intervention: a specific section will be devoted to this group, where main analyses will be repeated. The cut-off for statistical significance will be set at 0.05, two-tailed. Analyses will be carried out in blind using Stata/IC v. 15 or higher (Statacorp). A detailed Statistical Analysis Plan (SAP) will be written within 1 month after enrollment of the first patients.

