The 9-h time window has been inspired by recent clinical trials on recanalization therapies in acute ischemic stroke, such as EXTEND and WAKE-UP trials, that demonstrated potentially salvageable tissue up to 7–10 h from symptom onset, even in patients without large vessel occlusion (29, 32). The neuroprotective effect of RIC is presumably advantageous in presence of salvageable brain tissue, whose survival can last many hours after stroke onset depending on multiple factors. Many preclinical studies indicate that RIC helps the survival of salvageable brain tissue by reducing apoptosis, downregulating inflammatory response, and improving collateral circulation in the ischemic penumbra (33). Furthermore, two pre-clinical studies on a rat model of experimental ischemic stroke demonstrated that RIC is beneficial up to 6 h after ischemic stroke due to permanent large vessel occlusion (18, 19). Based on this evidence, we hypothesize that the application of RIC may be beneficial up to several hours after stroke onset in presence of salvageable brain tissue.

In a previous clinical trial (23), wherein penumbral salvage was the primary outcome and both infarct growth and final infarct size were secondary outcomes, no between-group differences were found in patients treated with RIC plus standard therapy and in those that received standard therapy alone. However, radiological findings represent surrogate outcomes allowing only indirect measurement of treatment efficacy and the lack of demonstration of a positive radiologic effect does not exclude a clinical benefit with certainty. Taking a different approach, in TRICS-9 a clinical outcome has been chosen to obtain a direct measure of RIC efficacy.

The primary outcome will be early neurological improvement, defined as NIHSS percent change at 72 h, following the definition adopted in a recent study that re-assessed the NINDS part 1 trial on intravenous thrombolysis in acute ischemic stroke (30, 31). This primary outcome has many advantages: (I) it accounts for the wide variation in admission scores across patients, (II) it is sensitive enough to allow a higher study power than that achievable using absolute changes in the NIHSS score, even with a relatively small sample size, (III) it is sufficiently hard to test a large effect size of immediate clinical interest, and (IV) the study power associated with a continuous outcome variable is expected to be higher than that achieved using a dichotomous outcome variable.

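### The data-driven median split of pain scores, and a logistic mixed model for rare symptomatic hemorrhage, may leave the tolerability and sICH comparisons without a usable estimate

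*Protocol article*

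**What the plan says.** The Data Analysis section plans "using a logistic mixed model to assess the effect of RIC on secondary variables" and names three of them: Wong-Baker pain, the modified Rankin scale (mRS) and sICH.

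- **Pain:** "Wong-Baker Face Pain Rating Scale scores will be dichotomized around medians". Under Outcomes, pain is measured twice, after the procedure and at 72 h. The text does not say whether the median is pooled or taken per arm, or where a score equal to the median goes.
- **sICH:** the SITS-MOST definition applies (Outcomes). No expected rate is given, and no alternative is named for the case of few or no events.
- **Control procedure** (Interventional Method): "Patients in the control group will have the blood pressure cuff placed around the non-paretic arm for 40 min but will undergo no inflations".
- **Size** (Sample Size Estimates): "An estimated total sample size of 80 patients (40 patients in each arm").

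The other secondary outcomes are handled differently. NIHSS change at 24 h and 48 h is compared by a Wilcoxon-Mann-Whitney test, feasibility is a proportion, and the biomarkers are shown as histograms.

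**The concern.** A cut-point taken from the observed scores means that the tolerability endpoint is undefined until the data are in, and it may differ between the two time points. On a coarse scale with many zeros, the median can sit at the floor:

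- **Split at or above 0:** every patient falls in one class and there is nothing to model.
- **Split above 0:** the outcome becomes any pain versus none. It can be analysed, but severity is lost, and severity is much of what tolerability means.
- **Each arm cut at its own median:** the two classes mean different things in the two arms, and the odds ratio no longer compares pain between them.

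For sICH the risk is sparse data. A logistic model, mixed or not, has no finite maximum-likelihood estimate of the treatment effect when one arm has no events.

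At stake are the between-arm tolerability comparison and the between-arm sICH comparison. Either could end in a failed fit, or in a method chosen after the data have been seen.

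**Working it through.** **Reproducing the plan's own figure.** The only stated calculation is for the primary outcome: "should yield 80% power to detect a clinically significant difference of 20% (40% in treatment vs. 20% in control arm"), "considering a standard deviation of 30"%, two-sided 0.05, Wilcoxon-Mann-Whitney. With Noether's formula, P(X<Y) = Φ(20/(30√2)) = 0.681, and N = (1.960 + 0.842)² / [3 × (0.681 − 0.5)²] = 79.6, that is 80. The figure reproduces. Nothing below touches it.

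**Pain.** Inputs: 40 per arm (Sample Size Estimates); no inflation in controls (Interventional Method). The documents give no pain distribution, so the shares scoring 0 are assumptions. With 80 patients the pooled median is the mean of the 40th and 41st ordered scores, so it is 0 exactly when at least 41 patients score 0. The number of zeros is Bin(40, p_C) + Bin(40, p_R), and the exact probability of 41 or more is:

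| Controls scoring 0 | RIC 10% | RIC 20% | RIC 30% | RIC 50% |
|---|---|---|---|---|
| 80% | 8% | 44% | 82% | 99.7% |
| 90% | 43% | 87% | 99% | >99.9% |
| 95% | 74% | 98% | 99.9% | >99.9% |

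The result turns on whether the expected number of zeros, 40(p_C + p_R), exceeds 40. It is 36 in the 80%/10% cell, the only one below 43%. At 72 h, long after cuff removal, the arms may be alike; if 60% of each score 0 (assumed), the probability is 96%.

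With a median of 0, an at-or-above split always fails. An above-0 split fails by separation only if all 40 controls score 0, which has probability p_C^40: 0.8^40 = 0.01%, 0.9^40 = 1.5%, 0.95^40 = 13%.

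**sICH.** With a common rate r (assumed) and q = (1 − r)^40, the probability that at least one arm has no events is 1 − (1 − q)², and the probability of no event at all is q².

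| Assumed rate r | q | At least one empty arm | No events in the trial |
|---|---|---|---|
| 1% | 0.669 | 89% | 45% |
| 2% | 0.446 | 69% | 20% |
| 3% | 0.296 | 50% | 9% |
| 5% | 0.129 | 24% | 2% |
| 8% | 0.036 | 7% | 0.1% |

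The 50% point lies at a rate of 3.0%. An exact interval exists at any count: for 0/40 the two-sided 95% Clopper-Pearson upper limit is 1 − 0.025^(1/40) = 8.8%.

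**The case against.** The case against has four parts.

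**Pain.** Total collapse needs an at-or-above rule that the protocol does not state. Under an above-median rule the split is interpretable and rarely separates. The plural medians may simply refer to the two time points, and tie handling is ordinary SAP detail; a SAP is announced. This stands as far as collapse is concerned: it is possible, not certain. It does not rescue the rule itself. The data-driven cut is stated in the protocol, and its best outcome at a median of 0 still discards severity.

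**sICH.** A reader might infer that the model will usually be inestimable. The documents do not support that, because they give no rate, and the statement holds only up to about 3%. The Discussion admits anticoagulated patients and large-vessel occlusions with early infarct signs, so a higher rate cannot be excluded. Crude rates can be reported whether or not a model converges, and a DSMB reviews safety separately. All of this stands. The point is a conditional risk to the model-based comparison, not a loss of safety reporting.

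**mRS.** A reader might also infer that splitting mRS is an error, since "The mRS scores will be dichotomized as a good functional outcome" (0–2) versus poor (3–6), while the Discussion argues that "the study power associated with a continuous outcome variable is expected to be higher than that achieved using a dichotomous outcome variable". That sentence defends the choice of the primary outcome. The mRS cut is conventional and fixed in advance for a secondary outcome, so preferring an ordinal analysis is a matter of choice.

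**Scope.** It would be wrong to say that the secondary outcomes in general are forced into logistic models: three of six are. Nor can one object to a random site effect on three centers here, because the random term for these models is not named.

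**Conclusion.** The point holds for two analyses.

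1. **Pain.** The median split is data-dependent, ambiguous and poorly suited to a scale on which uninflated controls are likely to score 0. A pooled median of 0 has probability 43% or more in 11 of the 12 assumed combinations, and 8% in the remaining one. The consequence ranges from an analysis that cannot be fitted to one that ignores severity, depending on a tie rule that is not given.
2. **sICH.** The planned model gives no finite treatment estimate with probability 89% at a 1% rate, falling to 24% at 5% and 7% at 8%. Rates are assumed equal in both arms.

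Every probability rests on assumed zero shares or event rates, since the documents supply neither. The mRS split is not an error, and the primary analysis and sample size are unaffected. The change is worth making because it is nearly free and gives a defined analysis whatever the data look like.

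**What to change.** Write into the SAP, and into the protocol at its next revision:

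- **Pain:** compare the full Wong-Baker scores between arms with a Wilcoxon-Mann-Whitney test, preferably stratified by site to match the randomization, separately after the procedure and at 72 h. Report the distribution of scores by arm at each time point. Drop the median split.
- **sICH:** report counts and proportions per arm with exact (Clopper-Pearson) intervals, and compare arms with Fisher's exact test or an exact interval for the risk difference, in place of the logistic mixed model.
- **mRS (optional):** an ordinal analysis may be added as a supplement to the planned 0–2 versus 3–6 split.

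The cost is wording only, with no extra data and no change in sample size. The small downside is that no covariate-adjusted odds ratio will be available for pain or sICH.

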### Outcomes

Admission NIHSS will be assessed before randomization, whereas NIHSS at 72 h (NIHSS72) will be obtained by a neurologist blinded to treatment allocation.

The primary efficacy outcome will be early neurological improvement at 72 h, defined as percent change in NIHSS score [(Admission NIHSS—NIHSS72) × 100/Admission NIHSS]. This definition has been adopted in a recent study that re-assessed the primary outcome of the NINDS part 1 trial on intravenous thrombolysis, wherein percent change in NIHSS score resulted to be more sensitive in demonstrating early clinical benefit and more predictive of long-term neurological outcome (30, 31) than the absolute changes in NIHSS score.

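### Setting every worsened patient to 0 at 72 h departs from the signed definition of the primary outcome and hides both the depth of worsening and the difference between stable and worse patients

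*Protocol article*

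**What the plan says.** Protocol article, Outcomes: early neurological improvement at 72 h is "defined as percent change in NIHSS score", with the formula 100 × (admission NIHSS − 72 h NIHSS) / admission NIHSS. This is positive for improvement and negative for worsening, and no lower limit is given. The Discussion repeats the percent-change definition, also without a limit.

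Protocol article, Data Analysis, for the primary outcome: "patients with neurological worsening will be given a percent change of 0". On deaths it adds that "those deceased within 72 h will be given the last percent change available", and that "a percent change of 0 will be assigned in case admission NIHSS is the only available data". The primary test is Wilcoxon-Mann-Whitney, and a mixed linear regression is the secondary analysis of the same outcome. The 24 h and 48 h percent changes are secondary outcomes with the same formula, and the reset to 0 is not extended to them.

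Protocol article, Sample Size Estimates: "An estimated total sample size of 80 patients (40 patients in each arm) should yield 80% power" for medians of 40% vs 20%, "considering a standard deviation of 30"%. The section does not say whether that SD is on the signed or the floored scale.

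**The concern.** The two sections describe different endpoints under one name. On the signed scale, a patient going from NIHSS 10 to 12 scores -20 and one going from 10 to 20 scores -100. Under the Data Analysis rule both score 0, as does a patient who stays at 10. No reason for the rule is given.

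Two things are at stake. The first is what the effect estimate means: a linear model fitted to floored scores does not estimate the difference in the percent change that the Outcomes section defines. The second is a mixed response. If RIC benefits some patients and makes others worse, the benefit counts in full and the deterioration counts only down to zero. The trial is meant to inform a possible phase III study, so this asymmetry matters even where the p-value is little affected.

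Blinding adds weight. The article describes blinded assessment only at 72 h and 3 months, so the one blinded NIHSS measurement is the one that is floored.

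**Working it through.** **Inputs.** From Sample Size Estimates: 40 per arm, 20 vs 40, SD 30. From Data Analysis: two-sided 0.05 and the Wilcoxon-Mann-Whitney test. Assumptions: normal shape, scores capped at 100% (the maximum possible improvement), and the harm scenarios below.

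**1. The plan's own figure.** Noether's formula: p = Φ(20 / (30√2)) = 0.681; N = (1.960 + 0.842)² / (12 × 0.25 × (0.681 − 0.5)²) = 79.6, rounded up to 80. The stated sample size reproduces.

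**2. Share of patients reset.** Controls: Φ(−20/30) = 25%. RIC: Φ(−40/30) = 9%.

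**3. Effect on the mean difference in the design case.** The floored mean is μΦ(μ/σ) + σφ(μ/σ).
- Control: 20 × 0.7475 + 30 × 0.3194 = 24.53; less 0.04 for the cap, 24.50.
- RIC: 40 × 0.9088 + 30 × 0.1640 = 41.27; less 0.25 for the cap, 41.02.
- Floored difference: 41.02 − 24.50 = 16.5.
- Signed difference with the same cap: 39.75 − 19.96 = 19.8.

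The difference in medians stays at 19.9, because both medians lie above zero.

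**4. Mean differences in assumed harm scenarios** (control signed mean 19.96, floored 24.50).
- *Mixed response:* 20% of RIC patients deteriorate by 50–100% (mean −75) and the rest gain 20 points. Signed: 0.2 × (−75) + 0.8 × 39.75 − 19.96 = −3.2. Floored: 0.8 × 41.02 − 24.50 = +8.3. Simulation gave −3.1 to −3.3 and +8.2 to +8.3.
- *Subgroup harm:* 25% of RIC patients deteriorate by 20–100% (mean −60) and the rest are as controls. Signed: 0.25 × (−60) + 0.75 × 19.96 − 19.96 = −20.0. Floored: 0.75 × 24.50 − 24.50 = −6.1.
- *Deeper worsening:* RIC triples the depth of any worsening. The mean of the negative part is 20 − 24.53 = −4.53, so the signed difference is 2 × (−4.53) = −9.1. The floored difference is 0.

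**5. Wilcoxon-Mann-Whitney rejection rates** (20,000 simulated trials, 40 per arm; where runs differed slightly, the range is shown).

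| Scenario | Signed | Floored |
|---|---|---|
| No effect (type I error) | 5.0–5.1% | 5.0% |
| Design case, 40 vs 20 | 81–82% | 81% |
| Uniform 20-point harm, 0 vs 20 | 81–82% | 77–78% |
| Subgroup harm (against RIC) | 46–47% | 31–32% |
| Mixed response (significant for RIC) | 11% | 18–19% |
| Worsening three times deeper | about 6% | about 5% |

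**The case against.** The case for leaving the rule alone has real parts.

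- *It is prespecified and symmetric.* It applies alike to both arms and suits an outcome named for improvement. Type I error is kept and design power falls by less than one point. This stands.
- *It may serve the linear model.* With admission NIHSS as low as 5, signed percentages can run to several hundred percent negative and dominate a regression. This is a plausible purpose, though the article does not state it. It does not justify flooring the rank-based primary test, which already limits the influence of extreme values.
- *Harm is recorded elsewhere.* The 3-month mRS, symptomatic intracerebral hemorrhage, the unfloored 24 h and 48 h scores and DSMB review of serious adverse events all catch some of it. This stands in part. The hemorrhage definition needs a Type 2 parenchymal bleed. The mRS is dichotomised at 0–2 vs 3–6, so further worsening within the poor category does not register. The article does not describe the 24 h and 48 h NIHSS as blinded.
- *A signed rank test would not see everything either.* In the scenario of worsening three times deeper, both versions reject at about the alpha level. The loss there concerns the mean and the linear model, not the primary test.

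A reader might infer that harm from RIC cannot be seen at all, or that half the response is discarded. The figures do not support this: a uniform 20-point harm is still detected in 77–78% of trials, and about 25% and 9% of patients are reset.

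A reader might also infer from the cited 24 h control figure (15 with SD 35) that the trial was powered on the wrong scale. On a 0–100 scale with mean 15 the largest possible SD is √(15 × 85) = 35.7, so that source figure is presumably signed. The trial, however, was planned on SD 30 at 20 and 40, where the limits are √(20 × 80) = 40 and √(40 × 60) = 49, and it was planned on medians, whose difference barely moves.

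**Conclusion.** The point holds as an inconsistency between two sections and as a poor choice of scoring rule. The floor removes from the primary outcome how far patients worsen and whether they are stable or worse. Under the planning values it shrinks the mean difference from about 20 to 16.5 points. In a mixed response it can change the sign of the mean difference, and it cuts the chance of detecting harm confined to a subgroup by about a third (47% to 31%). It does not invalidate the primary test, its type I error, the 80% power or N = 80.

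The shares reset and the shrinkage rest on a normal shape with SD 30. The harm figures rest on invented scenarios: they show what the rule can do, not what RIC is expected to do.

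**What to change.** In Data Analysis, drop the reset to 0 and analyse the signed percent change of the Outcomes section in the primary Wilcoxon-Mann-Whitney test, stating that the same definition applies at 24, 48 and 72 h. Keep the floored score as a labelled sensitivity analysis. Report the proportion of patients worsening by arm.

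Two consequences need handling in the same edit. First, signed percentages have a long left tail in the secondary linear model; one remedy is to model the 72 h NIHSS with admission NIHSS as a covariate. Second, without the floor, a patient who dies with only an admission score would keep a 0 and rank above a survivor who worsened, so the scoring of deaths should be made consistent with the signed scale, for example by giving deaths the worst rank.

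The cost is protocol or SAP wording, to be settled before unblinding. The sample size and stated power need no change: about 82% signed against 81% floored.

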### Allocation Concealment

This is an open label experimental study. Treatment allocation will be disclosed after patient recruitment, i.e., after inclusion/exclusion criteria have been recorded. Only outcome assessors (at 72 h and 3 months) and data analysts will be blinded after assignment to interventions.

